## Abstract

**Background:**

There is growing recognition that a sedentary lifestyle is being driven, at least in part, by environmental factors that affect individuals' physical activity choices and health behaviours. In other words, the environments in which we live, and with which we interact, have become ones that encourage lifestyle choices that decrease physical activity and encourage over-consumption of foods. However, evidence from community-led interventions to change local neighbourhood environments to support physical activity and healthy eating is lacking. This article summarises the research protocol developed to evaluate a community-led intervention *"My Health Matters" *aimed at reducing health inequalities relating to increasing physical activity and healthy eating as defined by community members *themselves*.

**Methods/Design:**

This study includes three of the most deprived electoral wards in Stoke-on-Trent. In each of these areas, environmental factors including proximity of physical activity spaces, greenspace and leisure facilities, neighbourhood connectivity and walkability, land-use-mix and population density, traffic, safety and crime, and food outlets will be mapped using Geographical Information Systems (GIS). A community postal survey of randomly selected addresses assessing environmental characteristics relating to physical activity, perceived health status, social capital, fruit and vegetable consumption and levels of physical activity will be undertaken (baseline and at 2 year follow-up). Based on baseline findings an intervention will be designed and implemented over a 2 year period that includes the following; use of community participatory research to build effective community partnerships; use of partnership consensus to identify, prioritise and design intervention(s) related to specific health disparities; recruitment of local residents to help with the delivery and sustainability of target intervention(s); and the development of local systems for ongoing monitoring and evaluation of the intervention(s).

**Discussion:**

A community-led and multidisciplinary approach to modifying environmental factors that support and reinforce healthful behaviours may be more successful than focusing on individual behaviour change as this approach does not exclusively rely upon individual will and capacity.

Study findings will be collated in 2012 and, if successful in improving levels of physical activity and healthy eating, will help to inform the design of a larger area-based, cluster randomized controlled trial to determine effectiveness.

## Background

There is growing recognition that the rising incidence of obesity is being driven by environmental factors that affect individuals' physical activity and dietary choices. The environments and neighbourhoods in which we live, and with which we interact, have become ones that, in the main, encourage lifestyle choices that decrease physical activity and promote overconsumption of foods. Previous research has identified broad features of the environment and neighbourhood that are likely to affect health outcomes. These include physical features of the environment (e.g. urban form [1], access to greenspace areas for play and active living [2], pedestrian network [3], active transport [4], access to fast food outlets [5]), provision of services (e.g. healthcare, education), socio-cultural/psychosocial (e.g. ethnic make up, level of social capital and community engagement [6]). There is a strong link between the built environment, health outcomes and inequalities. Research in obesity is moving away from individually orientated theories to broader, more environmentally based approaches for understanding and altering the wider environmental determinants of health behaviours [7]. The multiple, dynamic nature of those factors that might influence health are complex, especially for those who live in circumstances marked by social, economic and environmental disadvantages.

Recent debate about social inequalities in health has moved from what could be described as a Universalist approach to one that gives greater consideration to the importance of time and place [7,8]. The connections between social deprivation and ill-health occur in particular localities and in a particular period. Public health strategies designed to enhance health and reduce social inequalities need to be based within particular localities and take cognizance of social and cultural heritage [9]. However, the development of such strategies is complex, requiring both inter-sectoral collaboration and the active participation of local people in their design and implementation. Research in this area to date has been limited, focusing more on identifying the particular determinants of health rather than attempting to design and evaluate particular local solutions. This study is designed to contribute to this limited body of interventionist research.

While there is a huge body of literature that shows wide health inequities between groups or communities based on socio-economic deprivation, and more recently that "places and neighbourhoods" may be the way in which these inequalities are produced or reduced [10-12] there is very little clear evidence as to what types of interventions are most likely to reduce health inequalities. Place-based interventions re-emerged in public health in the 1980s when the Ottawa Charter [13] promoted the strategy of creating supportive environments that facilitate and support engagement with healthier behaviours. This gave rise to the WHO Healthy City movement where emphasis was placed upon reducing health inequalities through policy initiatives for improving the environment through social and economic change. However, difficulties in applying traditional research methods in evaluating these complex interactions has meant that there is little evidence-base of the impact of area-based community-led interventions. The health inequalities caused by this complex, ecological interaction of factors and conditions are not likely to yield to traditional, linear, causal chain, expert-driven approaches to problem solving. Therefore novel methodological and mixed-method approaches are required and as such, we have designed this pilot study to help meet some of these challenges and to inform a larger study, should its findings be positive.

Our approach aims to enhance the health of a community through promoting greater local involvement in community and health decision making to address the health needs and inequities experienced by the community. The establishment of such an approach within any community requires considerable engagement with the community and other agencies. An understanding of the various processes involved in the development and implementation of such a programme is essential if we are to maximize its transferability.

## Methods/Design

The "*My Health Matters*" project will run over 3 years and aims, in collaboration with local stakeholders in the UK health economy (Stoke-on-Trent Primary Care Trust, the Local Strategic Partnership, Stoke-on-Trent City Council, WHO Healthy City, Stoke-on-Trent Board and Third Sector organisations), to promote health in deprived inner city wards of Stoke-on-Trent, UK by undertaking a community-led intervention aimed at reducing health disparities and the associated environmental determinants related to those of the population who are sedentary and overweight/obese. The "*My Health Matters*" project will focus on adults (16+ years), rather than on children; however, families will be involved in the programme where appropriate.

### Study aims

The aim of our proposed study is to determine the efficacy of a community-led intervention in changing environmental determinants of lifestyle health behaviours by targeting barriers relating to increasing physical activity and healthy eating as defined by community members *themselves*. Information on process and effect size will be used to design a larger controlled trial should the findings be positive.

### Study design

Case study pre-post test intervention in three electoral Ward areas of similar socio-economic deprivation [14] in a deprived inner city in the UK with an estimated population of ~10,000 adults.

Targeted communities in these wards will take part in an intensive community-led project, designed to engage its residents in the development and delivery of a range of health related interventions over a period of 2 years. The intervention will:

1. use community participatory research to build an effective community partnership in order to engage community residents, and strengthen community involvement and participation

2. use partnership consensus to identify, prioritise and design intervention(s) related to specific health disparities (and their relevant environmental determinants and mediators)

3. recruit local residents and Third Sector organisations to help with the delivery and sustainability of the target intervention(s)

4. establish local systems for ongoing monitoring and evaluation of the intervention

5. establish a local Public Health Advisory Group comprised of members from cross-government departments (e.g. urban planning, architecture, health, police and transport) to help facilitate policy change

### Research hypothesis

It is predicted that a community-led intervention (working with the community and multiple agencies collectively to achieve beneficial change in a given factor) will increase the proportion of the target population who are physically active (taking part on at least 3 days/week in moderate intensity sport and active leisure) by 10% more (after a two year of intervention).

### Study population

Our study will include targeted lower level Super Output Area (SOAs), the smallest geographical unit for which census information is available in the UK, in three deprived wards in Stoke-on-Trent, UK (Meir, Burslem South and Bentilee) that are similar with regards to socio-economic status (i.e. in the most deprived 40% of the 2007 Index of Deprivation - (IMD)) and are not undergoing major housing regeneration over the next 3 years. A lower level Super Output Area consists of a population size of ~1,500. These spatial units were chosen because they provide an approximate neighbourhood level of analysis due to their population size and are tied to UK Census data.

### Proposed sample size

Sample size calculations for the independent survey sample are based on Cohen's arcsine transformation for estimating differences between proportions [15], where;

$$\begin{array}{c} \varphi =2\;\text{arcsine}\left(\sqrt{\text{p}}\right)\\ \text{h}=\left|\varphi_{1}-\varphi_{2}\right| \end{array}$$

P is the proportion and h is the effect size to be detected. The best available estimate of the population proportion currently active at the recommended level was that taken from Active People Survey 2 [16] (sub-group NS-SEC 6-8 i.e. those most closely matching the demographic profile of the target population for this study), which was 7.5%. Based on our previous research [17], we anticipate being able to achieve a 10% increase in this population proportion i.e. 17.5% after the community-led intervention. Using Cohen's arcsine formula this gives a standardised effect size of 0.273. Assuming a false positive error rate of .05, statistical power of .8 and this standardised effect size, we have calculated a required sample size of 283 participants at follow-up. Further, assuming a survey response rate of 10% (expected to be low for this target population) the issued sample size will be 2830 surveys.

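### The sample-size figures do not reproduce: 7.5% against 17.5% gives h = 0.308, not 0.273, and neither value gives 283 at alpha .05 and power .8

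*Protocol article*

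**What the plan says.** All the figures stand in one paragraph of the protocol article, under Proposed sample size. The method is named: "Sample size calculations for the independent survey sample are based on Cohen's arcsine transformation for estimating differences between proportions". The formula is printed: φ is twice the arcsine of the square root of p, and h is the absolute difference between the two φ values. The baseline proportion is 7.5%, from a national survey subgroup. The target is a "10% increase in this population proportion i.e. 17.5% after the community-led intervention", so the increase is 10 percentage points and not a relative 10%.

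The result given is that the "arcsine formula this gives a standardised effect size of 0.273". The next step reads "Assuming a false positive error rate of .05, statistical power of .8 and this standardised effect size", and from these inputs "we have calculated a required sample size of 283 participants at follow-up". A 10% response rate then turns 283 into 2830 issued surveys.

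The article does not state whether the test is one- or two-sided, or whether 283 is the number per wave or the sum over two groups.

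**The concern.** The formula, both proportions, alpha, power, effect size and sample size are all printed, so each step can be checked without any unseen document. Two steps fail independently: from the proportions to h, and from h to 283.

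The 283 fixes the size of the mailing. The Community survey and Primary outcome measures sections also claim that the study can detect a 10% difference. If the stated inputs do not lead to 283, a reader cannot tell what power the study was planned to have.

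**Working it through.** **Inputs** (all from Proposed sample size): p1 = 0.075, p2 = 0.175, alpha = .05, power = .80, stated h = 0.273, stated n = 283. Sidedness and per-group or total are not stated, so each is tried.

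**Step 1: effect size by the article's formula.**

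- φ(0.075) = 2·arcsin(√0.075) = 0.5548
- φ(0.175) = 2·arcsin(√0.175) = 0.8632
- h = |0.5548 − 0.8632| = 0.3084

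The stated 0.273 is about 11% lower (0.0354 / 0.3084). Working backwards, h = 0.273 from a baseline of 7.5% gives a target of sin²((0.5548 + 0.273)/2) = 0.162. For a 10-point rise, h = 0.273 needs a baseline of about 11.4%. Neither 16.2% nor 11.4% appears in the article. A relative 10% rise (7.5% to 8.25%) gives h = 0.028, so that reading does not explain it either.

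**Step 2: sample size at alpha .05 and power .80.** For two independent groups, n per group = 2(z_alpha + z_power)² / h². Two-sided, (1.960 + 0.842)² = 7.849; one-sided, (1.645 + 0.842)² = 6.183. Results before and after rounding up:

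| h | Test | n per group | Total |
|---|---|---|---|
| 0.273 | two-sided | 210.6 → 211 | 422 |
| 0.273 | one-sided | 165.9 → 166 | 332 |
| 0.3084 | two-sided | 165.05 → 166 | 332 |
| 0.3084 | one-sided | 130.01 → 131 | 262 |

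None is 283. Other variants at power .80 do not help:

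- A one-sample test needs 106 or 83 at h = 0.273 (two- or one-sided), and 83 or 66 at h = 0.308.
- The direct two-proportion formula gives 171 per group (342 total) two-sided and 135 (270) one-sided.
- With continuity correction that formula gives 190 (380) and 154 (308).

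The nearest figure is 270, which is 4.6% below 283 (13/283). It is one-sided and does not use the arcsine method.

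**Step 3: what 283 delivers at h = 0.3084.** Power = Φ(h·√(n/2) − z_alpha), with n per group.

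- 283 per wave, two-sided: 0.3084 × √141.5 − 1.960 = 1.709, so power is 95.6%.
- 283 in total (141.5 per group), two-sided: 0.3084 × √70.75 − 1.960 = 0.634, so power is 73.7%.
- 283 in total, one-sided: 82.9%.

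At the stated h = 0.273 the two-sided values are 90.1% per wave and 63.2% as a total.

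**Step 4: where 283 might come from.** With h = 0.273, two-sided alpha .05 and power .90, n = 2(1.960 + 1.282)² / 0.273² = 282.0 per group. This is close, but not 283. Splitting alpha over three comparisons with power .80 at h = 0.273 gives about 281. The article mentions neither.

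**Step 5: the mailing.** 283 / 0.10 = 2830. This division is correct, but it carries the unreproduced 283 forward.

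**The case against.** The strongest reply is that the error does no harm. The wording refers to participants at follow-up, which most naturally means one wave. On that reading 283 exceeds every requirement in the Step 2 table that is counted per group, and nominal power at h = 0.308 is about 96%. The study describes itself as a pilot, and no mailing number would change. This stands, and it limits the severity. It does not rescue the figures: the paragraph still attributes to power .8 and h = 0.273 a number that they do not produce.

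It may also be said that h could be right and the proportions misprinted. The article cannot exclude this, so the fix must allow for it. Since 7.5% and 17.5% are the stated inputs, 0.308 is the natural correction.

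Three stronger readings are tempting but not supported:

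- **That the study is underpowered.** This follows only if 283 is a two-group total and the test is two-sided, and the article states neither. The opposite claim, that the sample is certainly too large, rests equally on the unstated per-wave reading.
- **That the calculation was really run at 90% power.** The match is close (282), but a three-way alpha split comes nearly as close (281). The origin is an inference.
- **That the wrong h will be passed to the larger trial.** Study aims refers to effect-size information that this study will produce, not to the planning value.

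**Conclusion.** Wrong as written, of moderate severity. The stated proportions give h = 0.308 where the article has 0.273, and no standard version of the calculation at alpha .05 and power .8 gives 283 from either value.

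The size and direction of the consequence depend on a point that the article leaves open. If 283 is per wave, it is 34% above the two-sided need at the stated h (283/211) and about 70% above that at the recomputed h (283/166), and the stated .8 is not what the design delivers. If it is a two-group total, two-sided power falls below .8.

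These powers assume simple random, independent and unweighted samples. The Community survey section plans selection weights and sends the second questionnaire to wave 1 respondents, so 96% is a nominal figure and not a demonstrated margin.

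**What to change.** In Proposed sample size:

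1. Correct h to 0.308; or, if 7.5% and 17.5% were not the proportions used, correct those and recompute h.
2. State whether the test is one- or two-sided, and whether 283 is per wave or a total.
3. Either state n = 166 per wave for 80% two-sided power under simple random sampling, or keep 283 and restate the power it delivers. Show any design effect, attrition allowance or multiplicity adjustment that 283 was meant to contain.

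If 283 is per wave, the cost is wording only, and this error gives no reason to change the 2830 surveys. (At a 10% response, 166 per wave would correspond to 1,660.) If 283 proves to be a two-group total and the test two-sided, the number to be issued must be reconsidered.

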### Study components

The study will be conducted in 4 overlapping phases over a total of 3 years.

### Phase 1: Baseline -mapping of the built environment and community survey using Geographical Information Systems (GIS)

During Phase 1, novel datasets will be assembled that contain data from existing local, regional and national databases together with data from the Regional Library, Public Health Observatory and Ordnance Survey. Within each ward we will map data at the unit of lower layer Super Output Area (LSOA) neighbourhood. LSOAs consist of 4-6 output areas (OAs) which are the building blocks for the 2001 Census. Each SOA has a minimum population of 1,000 and a mean population of ~1,500. SOAs have the following advantages: (a) they are ultimately composed of groups of postcodes and so facilitate better linkage with other datasets that have postcodes, (b) they provide 100% coverage for a range of socio-economic data from the census, (c) the same unit was used for the Index of Multiple Deprivation 2007 and (d) they will be the standard unit for collection of National Statistics and so provide links with other datasets.

For each LSOA population within the wards, we will map a number of key environmental indices that have been identified from the literature to potentially impact on levels of physical activity and eating [18]. These include;

• Population density

• Access to green space

• Access to local services, shops and food retail (including fresh food retail and "fast" foods)

• Access to physical activity facilities (indoor/outdoor)

• Street connectivity

• Land use mix

• Road traffic levels

• Road traffic accidents (including pedestrians and cyclists)

• Crime and anti-social behaviour

All of the above measures will be calculated around every residential address within the study areas. They will be reported within a defined neighbourhood boundary representing a pedestrian catchment area. These neighbourhood boundaries will be created by measuring a 500 m and 1 kilometre walking distance along all roads and pathways from each residential address. A full description of the methodologies, using Geographical Information Systems (GIS) to create these boundaries [19], and the data sets used can be found in a separate technical report [20].

### Community survey

Addresses will be selected from the postcode address file representing all of the targeted streets within each ward included in the study. Postal questionnaires will be sent to a random sample of addresses within the study area for each of the Lower Super Output Areas (LSOA). For each household a random date will be generated and the adult whose birthday falls closest to this date will be asked to complete the questionnaire (intended to select persons within the household with equal probability).

As an incentive, all participants will be entered in to a prize draw for £200 of High Street vouchers if they complete and return the questionnaire.

All respondents at wave 1 would be issued again at wave 2 (at 24 month follow up). This gives sufficient power to detect the expected 10% difference in population proportions. Since only one person is being randomly selected at addresses which have more than one resident aged 16+, at the analysis stage we would apply weights (equal to the inverse probability of selection) to adjust for this.

The self-report questionnaire will include validated and reliable questions on physical activity [21], behavioural intentions and behavioural change [22], perceived health - SF12 [23], perceptions of the local neighbourhood for physical activity (Neighborhood Environment Walkability Scale) [24], social capital [25] and socio-demographic information (gender, age, ethnicity, education level, household tenure). The questionnaire and survey procedures will be fully piloted before the main fieldwork for wave 1 and for any changes or additional questions at wave 2 (at follow up).

In addition to the survey a random sub-sample of 100 adults from each of the three Wards will be asked to wear an accelerometer (GMT1) for 7 consecutive days to measure physical activity levels [26].

Results from the objective GIS mapping and community survey will be used as the basis of community consultation.

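### 2830 surveys at a 10% response give about 283 people at wave 1, but the plan requires 283 at follow-up and describes wave 2 as a re-issue to wave-1 respondents, with no retention allowance and an independent-samples calculation

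*Protocol article*

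**What the plan says.** The Proposed sample size section of the protocol article sets the basis: "Sample size calculations for the independent survey sample are based on Cohen's arcsine transformation for estimating differences between proportions". It takes a starting proportion of 7.5% and writes "we anticipate being able to achieve a 10% increase in this population proportion i.e. 17.5% after the community-led intervention". It gives an effect size ("Using Cohen's arcsine formula this gives a standardised effect size of 0.273"), a false positive rate of 0.05 and power of 0.8, and concludes "we have calculated a required sample size of 283 participants at follow-up". It then assumes a 10% survey response, which it expects to be low in this population, and arrives at 2830 issued surveys.

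The Community survey section describes a postal survey to randomly chosen addresses and then the second wave: "All respondents at wave 1 would be issued again at wave 2 (at 24 month follow up". The next sentence reads "This gives sufficient power to detect the expected 10% difference in population proportions". The section gives no wave-2 response or retention rate and mentions no new address sample for wave 2. The Abstract says that the survey is run at baseline and at two years, but not whether new addresses are drawn.

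**The concern.** The two sections do not describe the same study. One needs 283 people at the end and allows for one round of non-response. The other spends that allowance at the start, because the 10% applies to the first mailing and the second goes to those who answered it. Nothing is left for people who move, cannot be traced or do not reply 24 months later.

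The label is also inconsistent. The change from 7.5% to 17.5% is a before/after change in one population. If it is measured by re-surveying the same people, the two waves are correlated, and a formula for two independent samples is not the right one for that contrast.

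What is at stake is the follow-up size and the assertion of adequate power that is attached directly to the re-issue. That assertion depends on a retention rate and a within-person correlation, and the article gives neither.

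**Working it through.** **Inputs from the article:** p1 = 0.075, p2 = 0.175, stated h = 0.273, alpha = 0.05 (sidedness not stated; two-sided used here), power 0.80, response 10%, 283 at follow-up, 2830 issued.

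**Assumed, because the article does not give them:** retention of 80%, 60% or 40%, and a within-person correlation of 0.3.

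**1. The plan's own figures.**
- Issued surveys: 283 / 0.10 = 2830. This reproduces.
- Effect size: 2·arcsin(√0.175) − 2·arcsin(√0.075) = 0.863 − 0.555 = 0.308, not 0.273.
- Size per group, n = 2·((z_alpha + z_power)/h)²: with h = 0.273 and 80% power, 2·((1.960 + 0.842)/0.273)² = 210.6, so 211. With h = 0.308 it is 166. The 283 does not follow from the stated inputs. It is close to the result for h = 0.273 at 90% power, which is 282.

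**2. What the mailing delivers.** Wave 1: 2830 × 0.10 = 283. Wave 2: 283 × retention = 226, 170 or 113 at 80%, 60% or 40%. It equals 283 only at 100% retention.

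**3. Power with completers in both waves, treated as independent.** Power = Φ(h·√(n/2) − 1.960). For example, with n = 170 and h = 0.273: Φ(0.273 × 9.220 − 1.960) = Φ(0.557) = 71%.

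**4. Power for paired data (McNemar, normal approximation).** With correlation 0.3:
- Active at both waves: p1·p2 + 0.3·√(p1·(1−p1)·p2·(1−p2)) = 0.0131 + 0.3 × 0.1001 = 0.0431.
- Discordant proportions: 0.075 − 0.0431 = 0.0319 and 0.175 − 0.0431 = 0.1319. Their sum is ψ = 0.1637 (from unrounded values), and their difference is δ = 0.10.
- Power = Φ((δ·√m − 1.960·√ψ)/√(ψ − δ²)) for m pairs.

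| Assumed retention | Wave-2 n | Independent, h = 0.273 | Independent, h = 0.308 | Paired, correlation 0.3 |
|---|---|---|---|---|
| 80% | 226 | 83% | 91% | about 96% |
| 60% | 170 | 71% | 81% | about 90% |
| 40% | 113 | 54% | 64% | about 75% |

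**5. Retention at which 80% power is still kept.**
- Independent formula: 211/283 = 75% at h = 0.273, and 166/283 = 59% at h = 0.308.
- Paired: 174 pairs at correlation 0 (61%), 142 at 0.2 (50%), 127 at 0.3 (45%).

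**The case against.** The strongest reply is that a closed panel is an inference. The article says that wave-1 respondents are issued again, not that nobody else is. A re-issue combined with a fresh sample would fit the words about independent samples and the 283 at follow-up. This stands as far as it goes: the article is ambiguous. But no second sample is described, and the sufficiency claim is tied to the re-issue, so the sections need reconciling on either reading.

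The second reply is that missing 283 is not the same as missing power. This also stands. At the stated 80% power, 283 is more than either effect size requires, and positive correlation lowers the requirement further. The independent-samples columns above are also on the low side, because they discard wave-1 respondents who are later lost. Keeping all 283 at wave 1 against 226, 170 or 113 gives 86%, 80% or 69% at h = 0.273 and 93%, 89% or 79% at h = 0.308.

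Third, a reader might infer that a panel is the wrong design because it leaves out people who move into the area. The article does not support that. Its Primary outcome measures section defines the outcome by people's change from their own initial activity level, and that can be measured only by following the same people.

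Finally, this is a pilot reported in a condensed article, and tracing procedures belong in the full protocol. That excuses missing procedural detail. It does not excuse a stated follow-up size that the described mailing cannot reach without complete retention.

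**Conclusion.** The inconsistency is real. As described, 2830 surveys give about 283 people at wave 1 and 283 × retention at wave 2, so the required 283 at follow-up needs 100% retention. The independent-samples basis does not match a before/after change measured on the same respondents. Both conclusions assume that wave 2 consists of the re-issued wave-1 respondents, which is what the text describes but does not say exclusively.

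A reader might go further and infer that the study is underpowered. The documents do not support that. Across assumed retention of 80% to 40%, power runs from 83% to 54% with the stated effect size and completers treated as independent, and from about 96% to 75% when paired with correlation 0.3. Whether power reaches 80% depends on two quantities that the article does not state. The claim of sufficient power is therefore unsupported as written, but it is not shown to be false.

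The calculation concerns the before/after change only. It does not size the comparison with the rest of Stoke-on-Trent in the Primary outcome measures and Data analysis sections, which is between separate groups.

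**What to change.** - State that wave 2 is a panel of wave-1 respondents. If a fresh sample is intended, say so and reconcile the Proposed sample size and Community survey sections.
- For the panel, restate the size as about 283 at wave 1 and 283 × an explicit retention assumption at wave 2.
- Recompute power for the before/after change with a paired formula over a stated range of retention and correlation. Correct the effect size to 0.308 if 7.5% and 17.5% are kept.
- Make the sentence on sufficient power conditional on those assumptions.
- Analyse the before/after change with a method that accounts for repeated measures on the same person, such as McNemar's test or a marginal model with person-level clustering. Keep the planned between-area comparison alongside it, since a paired test does not replace it.

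The cost is rewording, a short recalculation and one analysis choice. No additional mailing is needed.
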